### Type of study

This is an observational, longitudinal and prospective study.

### Population

People aged ≥75 years, will be recruited from different clinical and social settings, including acute geriatric wards, geriatric outpatient clinics, primary care centers and nursing homes.

### Inclusion criteria

Participants over 75 years of age, will be consecutively selected, who have signed the informed consent and accepted their voluntary participation.

### Exclusion criteria

General exclusion criteria are:○ MMSE score ≤ 20 points.○ Terminal illness (life expectancy ≤6 months).A Barthel Index < 90 in patients from the Acute Geriatric Unit, Outpatient Geriatric Consultation and primary care centers.A Barthel Index < 40 in residents from nursing homes.

### Recruitment process and sample size

Prior to the start of the recruitment process, Ethics Committee approval and any other regulatory approvals will be obtained.

Potential candidates will be assessed by geriatricians or other suitably qualified members of the study team and will provide information to each participant about the study and their participation. After each participant has read the participant information sheet and given written informed consent to participate, their eligibility criteria will be assessed and if satisfied, will be enrolled into the study. The participant’s right to decline their participation in the study at any stage without any explanation will be respected. The participant can withdraw the study at any time without giving reasons and with no detriment in their usual medical care. If a participant withdraws from the study after a prior inclusion, this information will be passed immediately to the principal investigator and the procedure for their exclusion will take place.

Each one of the participating centers has a scientific interest in the field of frailty (Table 1). The participants will be recruited in Spain, Italy, France, United Kingdom and Poland.

**Table 1 Tab1:** Participating centers

Country	Participating center
Spain	Fundación para la Investigación Biomédica del Hospital Universitario de Getafe (FIB-HUG)
Italy	Centro Medicina dell’Invecchiamento (CEMI)/ Università Cattolica del Sacro Cuore
France	Gérontopôle de Toulouse
United Kingdom	Aston University^a^
Poland	Department of Internal Medicine and Gerontology (DIMG) and Division of Internal Medicine of the University Hospital of the JUMC

^a^Aston University replaced Diabetes Frail Limited (DIFRAIL) in United Kindgdom as participating center

Contact with hospitals, primary care and nursing homes will be made through the coordinators of the corresponding Health Centers, requesting the authorization for the recruitment process and signing the proper documents to formalize their participation.

In order to determine the sample size, we have used two assumptions:The sample size is calculated according to the methodology of Peduzzi et al. [21] for a model of 4 variables. The variables included are: age, gender and Charlson index as covariates and frailty status as the main independent variable of interest.The outcomes to be assessed will be death, falls, disability and deterioration in cognitive function. Among these variables, death is the least frequent and generates the highest sample size therefore it can be used for the other three outcomes.Although there are some little differences in the mortality rates among the five European countries that participate in this project; the mean mortality rate for people aged ≥75 years in these countries is 10% annually. Therefore, in 18 months it will be 15%, which is the follow-up period forecasted in FRAILTOOLS project.

Within these assumptions the lower limit of the 1-α confidence interval for the accepted number of success is 355 and 388 participants in each setting of care for 95 and 99% CI, respectively. This number must be increased with the forecasted lost to follow-up, in 20%. As a whole, the final sample size is established in 485 persons per setting, which means a final figure of 1940 persons. Thus, every partner will be responsible for the enrolment, assessment and follow-up of 388 older adults (97 per setting).

### Follow-up

The follow-up will be of 18 months as maximum. In order to avoid memory bias, a phone call will be made in month 6 after the inclusion to assess whether there has been a fall or death. At 12 and 18 months, a personal interview with each participant will take place to register data on functional status (SPPB, Barthel and Lawton indexes), cognitive status (MMSE) and frailty status (Fried Frailty Phenotype Criteria, o Frailty Trait Scale – short version, SHARE-FI scale, 35-Items Rockwood Frailty Index, Clinical Frailty Scale, FRAIL scale and Gérontopôle Frailty Screening Tool) (Table 2).

**Table 2 Tab2:** Flow of the study

Time point	Baseline T1	Follow up		
		Month 6 T2	Month 12 T3	Month 18 T4
ENROLLMENT:				
Eligibility screen	X			
Informed consent	X			
ASSESMENTS:				
Socio-demographic data	X		X	X
Charlson Comorbidity Index	X		X	X
Barthel Index	X		X	X
Lawton Index	X		X	X
SPPB	X		X	X
MMSE	X		X	X
Fried’s Frailty Phenotype Criteria	X		X	X
Frailty Trait Scale – short version	X		X	X
SHARE Frailty Instrument	X		X	X
35-Items Rockwood Frailty index	X		X	X
FRAIL scale	X		X	X
Gérontopôle Frailty Screening Tool	X		X	X
Clinical Frailty Scale	X		X	X
OUTCOMES:				
Disability	X		X	X
Mortality		X	X	X
Falls		X	X	X
Incident cognitive impairment	X		X	X

In case a participant passed away during the follow-up phase of the study, the information will be recorded in the eCRF of the follow-up visits at 6, 12 or 18 months. A document to record death will be filled as an adverse event unrelated to the study. Data regarding mortality will be obtained from the official register of the country of the corresponding partner.

The principal investigator will ensure that the study takes place according to the protocol, to Good Clinical Practice principles, and to the Declaration of Helsinki of 1996. At the baseline visit, frailty assessment tools will be completed. Variables such as socio-demographic data, comorbidities, functional and cognitive status will also be assessed.

The Investigator will ensure that this study is conducted in accordance with the protocol, the principles of the Declaration of Helsinki, International Conference of Harmonization Guidelines for Good Clinical Practice and in full conformity with relevant regulations.

All substantial amendments to the original approved documents will also be sent to the appropriate Ethics Committee and Regulatory Authority (if applicable) for their revision.

The study staff will ensure that the subject’s anonymity is maintained. The subjects will be identified only by a subject code in the eCRF and any electronic database. All documents will be stored securely and only accessible by study staff and authorized personnel. The study will comply with the Data Protection Legislation in each country.

Subjects will not receive any economic compensation for participation in this study.

### Questionnaires and tools assessed

In the Query-Case Report Form the following information will be collected:Socio-demographic data: age, gender, race, marital status, education, cohabitation, need for caregiver, setting in which the subject is recruited, country of origin.Comorbidities:○ Charlson Comorbidity Index [22]: This scale predicts the ten-year mortality for a patient by classifying or weighting comorbid conditions. It consists of 19 issues each of which was weighted according to their potential influence on mortality.Functional status:○ Barthel Index [18]: Functional assessment scale that measures the subject’s capacity to perform ten activities of daily living in an independent manner.○ Lawton Index [17]: Instrument to assess the individual’s capacity to perform IADL independently. These skills are considered more complex than the basic activities of daily living as measured by the Barthel Index.○ Short Physical Performance Battery [23]: Test designed to measure functional status and physical performance by combining the results of the gait speed, chair stand and balance tests.Cognitive status:○ Mini Mental State Examination – MMSE [20]: It is a widely used test to screen patients for cognitive impairment and to track changes in cognitive functioning over time. It evaluates seven cognitive domains including orientation to time and place, repetition, verbal recall, attention and calculation, language and visual construction.Frailty assessment scales:○ Fried’s Frailty Phenotype Criteria [3]: Well-known scale to diagnose frailty. It is based on the biological causative theory and shows predictive validity for poor health outcomes across a wide range of illnesses and procedures. This tool combines a total of five variables, three of them self-referred: weight loss, exhaustion and reduced physical activity; and other two objective variables: weakness assessed by grip strength, and slowness measured by gait speed.○ Frailty Trait Scale – short version [24]: Scale that emerged from a population study in Toledo, Spain. It evaluates three dimensions: nutrition (BMI), physical activity (PASE), and nervous system (balance test).○ SHARE Frailty Instrument (6,7): Screening instrument for frailty proposed for the primary health care setting. It explores five dimensions: exhaustion, loss of appetite, weakness measured by grip strength, difficulty walking and low physical activity.○ 35-Items Rockwood Frailty index [25]: Scale with 35 items, based on data routinely collected as part of a geriatric assessment. It includes items on chronic diseases, basic and instrumental disabilities in activities of daily living, serum vitamin D, cognition, physical performance, nutrition, visual and hearing impairment.○ FRAIL scale [26]: Self-assessed short questionnaire, taking into account five different aspects: Fatigue, Resistance, Ambulation, Illness and Loss of weight. It does not require measurements or administration by healthcare professionals.○ Gérontopôle Frailty Screening Tool [27]: It is a short questionnaire addressed to primary care physicians with a total of six questions assessing the individual’s social, physical, functional and cognitive situation. There is no clear cut-off point to classify the patient as frail or not.○ Clinical Frailty Scale o Rockwood modified [28]: Scale that uses clinical descriptors and pictographs to stratify older adults according to level of vulnerability. It mixes items such as comorbidity, cognitive impairment and disability. According to the authors, it provides predictive information about mortality or institutionalization similar to that of other established tools.

The study is ongoing. Follow-up visits finished on November 30th. Statistical analysis will be run until April 1st, 2019. The publication of the full results will take place on the second half of 2019.

### Statistical analysis

FRAILTOOLS aims to 1) assess the selected instruments (scales) for both screening and diagnosis purposes in each of the four settings: acute geriatric wards, geriatric outpatient clinics, primary care centers and nursing homes; and 2) explore the sequential or consecutive assessment of the older population amongst settings.

Regarding the first objective of the analysis, we will assess the associations of each of the seven scales with the outcome for each setting and outcome through logistic regressions using age, sex and Charlson index as possible confounders. With these variables, we will construct three logistic regression models: unadjusted, adjusted by age and gender, and adjusted by age, gender and Charlson Index. Firstly, we will compute the classification performance (sensitivity, specificity, ROC curve, AUC, predictive values, likelihood ratios) for each model. This way, we will assess the most accurate scale for both screening (the most sensitive tool) and diagnostic purposes (the most specific tool), for each setting and for each outcome. Secondly, we will study the feasibility of the models, considering the time needed for the scale and the percentage of patients that can be evaluated per case.

Combining both outcomes by creating an index (classification performance * proportion of evaluated patients), we will determine the best scale (maximum value of the index) per setting for both screening and diagnosis. Thirdly, we will evaluate the sensitivity to change of the scales and the covariance of the scales with other measures as the SPPB through a mixed linear model.

For the second objective, we will first analyze the external validity of each model by using the data of each setting in the other models during the last phase of the project. Afterwards, we will evaluate which set of instruments is more appropriate for sequential or consecutive assessment when patients move between different settings: e.g. from nursing homes to geriatrics wards.

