Multiple studies have been undertaken worldwide to establish the prevalence of frailty [3, 7–9]. The data vary according to countries reaching a percentage of up to 27.3%. A survey of 7510 community-dwelling older adults in 10 European countries found that the prevalence of frailty was higher in southern than in northern Europe [7, 10]. For instance, in Spain the prevalence of frailty was 8.4% among institutionalized and community dwelling persons from rural and urban settings [8]. In Italy, in community-dwelling older adults the frailty prevalence was 13.9% [11]. In the French population older than 55 years-old and free of disability, around 25% are either frail or multimorbid [12]. In the nursing home setting this prevalence doubles in comparison with community dwelling people, reaching 68.8% according to a number of American studies [9, 13]. As frailty is highly associated with age, we should expect an increase in the number of new cases (incidence) of frailty as the European population gets older. Published data ranges from 4% new cases in adults aged over 65 years in Germany to 8% in adults aged over 60 years in Spain after three years of follow-up [14].

Dozens of scales and questionnaires have been used in the detection of frailty [15].; however a universal operational definition of frailty or a generalized method for its screening and diagnosis is still lacking [16]. In different clinical scenarios where the care of the elderly is a priority, such as primary health care or nursing homes, it is imperative to have specific instruments in the detection of frailty according to the characteristics of each level of care.

The FRAILTOOLS Project addresses the needs to validate scales for its application in different clinical and social settings, and its integration in management algorithms for the frail older patient.

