#### Secondary objectives

Establish the scale with the highest predictive value according to the most common adverse outcomes in frail patients.Design frailty detection algorithms according to the clinical setting.

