#### Secondary outcomes

**Performance** of the instruments by clinical setting: seven frailty assessment tools will be used in four different levels of care. The performance of each scale in the classification of frailty will be established.**Feasibility** composed by two main conditions: the percentage of people that are assessed by each tool in each setting (adequacy) and the time for carrying out the tool assessment. The utility of both screening and diagnostic tools stems, among other characteristics, from the time needed to pass them. This characteristic is relevant mainly in settings where the demand for attention is high and the time to provide is limited.**Sensitivity to change**, one of the problems of many of the tools used to assess frailty is that they have a low sensitivity to change. This is a relevant issue in clinical settings, where monitoring the progress of the patient is of high value. For this purpose, we will evaluate the change in the assessment level of patients observed at 12 and 18 months with each of the tools and their correlations with the changes observed in the functional status of the patients as assessed by SPPB.**Qualification as screening and/or diagnosis tool**: evaluate the utility of each scale as a frailty detection method, using pre-established criteria, based on the prevalence of this condition in each setting and the classification performance (Sensitivity, Specificity, Positive and Negative Predictive Values and Likelihood ratios), plus its feasibility, and its sensitivity to change.

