## Discussion

Frailty is the main risk factor for the appearance of disability [29]; once disability arises, recovery is unlikely [30]. Frailty can be reversed spontaneously [29, 31] or by exercise-based interventions [32].

In view of its prognostic power to cause disability, its high prevalence and potential reversibility, frailty is the ideal objective to approach the disability challenge in our elders [29, 31].

Many studies have demonstrated the utility of certain assessment tools to evaluate frailty in populations, however, the individual risk for disability has not been properly evaluated, which is the main interest in the daily clinical and social settings [14, 33]. Indeed, so far, no published studies have validated the usefulness and feasibility of frailty tools in geriatric units, primary care centers and nursing homes; where the prevalence of people with frailty is high and the risk to develop disability is palpable. FRAILTOOLS study will contribute to validate tools to screen and diagnose frailty in different clinical scenarios; with the purpose of implementing it in daily practice and creating diagnostic algorithms according to the setting assessed.

Therefore, it can be said that the FRAILTOOLS project is an *original* initiative; *relevant*, by focusing its efforts on the main risk factor for disability; *pertinent*, concentrating on providing screening and diagnostic tools for frailty in settings where its prevalence is the highest and where efforts in prevention could make a significant change in the trend towards disability. FRAILTOOLS also contributes to the initiative of the European’s Commission on Frailty, Integrated care and multi-chronic conditions by: 1) the application of coordinated and innovative preventive measures, 2) development and implantation of screening and early diagnostic programs of frailty, which include the optimization of functional capacity and the development of guidelines to manage frailty, 3) improve healthcare systems, 4) implement health promotion strategies, and 5) facilitate the exchange of Good Clinical Practice and expanding knowledge networks, and 6) promote innovation in healthcare at European level.

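### The best scale is chosen as a bare maximum within each setting, and no analysis tied to that choice estimates whether the ranking of scales differs between settings

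*Protocol article*

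**What the plan says.** The Secondary outcomes section states that "seven frailty assessment tools will be used in four different levels of care". Under Statistical analysis, "we will assess the associations of each of the seven scales with the outcome for each setting and outcome through logistic regressions". Sensitivity decides for screening and specificity for diagnosis. Classification performance is multiplied by the proportion of patients who could be evaluated, and with that index "we will determine the best scale (maximum value of the index) per setting for both screening and diagnosis". The rule uses point values; no margin or measure of uncertainty is attached to it.

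The result is meant to be specific to the setting. A secondary objective reads "Design frailty detection algorithms according to the clinical setting", the Background holds that "it is imperative to have specific instruments in the detection of frailty according to the characteristics of each level of care", and the Discussion speaks of "creating diagnostic algorithms according to the setting assessed".

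One cross-setting analysis is planned, under the second analysis objective (sequential assessment): "we will first analyze the external validity of each model by using the data of each setting in the other models". It is not linked to the choice of the best scale.

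**The concern.** Recommending one tool for wards and another for primary care is a statement about a difference between settings. Four separate maxima do not supply that contrast. They will differ whenever sampling error is large relative to the true gaps between scales, even if the scales rank identically everywhere.

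The external-validity step does not fill the gap. A model can transport badly because baseline risk differs while the order of the seven scales is unchanged, and it can transport well while the order changes. For an unadjusted model with one scale as a linear term, predicted risk is a monotone function of the scale. Its AUC in another setting is then simply that scale's own AUC there (if the sign of the association is the same), so transport adds nothing about ranking.

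At stake is whether the final algorithms reflect real differences between settings or noise. Confidence intervals around each setting's winner would not settle this: a clear winner in one setting and an unclear one in another is not evidence that the rankings differ.

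**Working it through.** **Inputs from Recruitment process and sample size.** A model of 4 variables; 15% mortality at 18 months; 355 or 388 evaluable per setting (95% or 99% CI); 20% loss; 485 enrolled per setting, 1940 in all.

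**Reproducing the plan's figures.** I assume 10 events per variable (inferred, not stated), so 4 × 10 = 40 events. The required n is the smallest with n × 0.15 − z × √(n × 0.15 × 0.85) ≥ 40.
- n = 355, z = 1.96: 53.25 − 1.96 × 6.73 = 40.06.
- n = 388, z = 2.576: 58.2 − 2.576 × 7.03 = 40.08.
- 388 / 0.80 = 485, and 4 × 485 = 1940.

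All figures reproduce. They size one model in one setting, not a comparison of scales or settings. Expected deaths per setting are 388 × 0.15 = 58.2.

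**Equal scales.** If seven scales perform identically and settings are independent, each scale is equally likely to win in each setting.
- P(one scale wins all four) = 7 × (1/7)^4 = 1/343 = 0.29%.
- Expected number of different winners = 7 × (1 − (6/7)^4) = 3.2.

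This result does not depend on sample size or event rate.

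**Simulation for mortality, AUC only.** Assumed: binormal scores, 388 per setting, 15% deaths, inter-scale correlation 0.5 to 0.7, the same true AUCs in all four settings, 1,500 trials per scenario.
- All AUCs 0.68: one scale wins all four settings in 0.1 to 0.4% of trials.
- One scale 0.72, six at 0.68: one scale wins all four in about 11 to 24%. The truly best scale is picked in 57 to 71% of single settings, against 93 to 98% when AUCs are averaged over settings.

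**Sensitivity of these figures.**
- Base AUC 0.70, correlation 0.4 to 0.8: a uniform advantage of 0.03 gives agreement in 3 to 21%; an advantage of 0.05 gives 19 to 74%.
- Event rate 35% (assumed), 0.72 against 0.68: agreement rises to about 32 to 55%.
- AUC multiplied by assumed completion rates from 98% down to 80%, the same in every setting: 18 to 31% with equal AUCs, and 78 to 92% with one better scale (0.72 against 0.68) that is also the most completed.

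**Noise in the protocol's own criteria.** With 58 deaths, the SE of a sensitivity of 0.70 is √(0.7 × 0.3 / 58) = 0.060, larger than the AUC's 0.037 to 0.041. With 388 − 58 = 330 survivors, the SE of a specificity of 0.70 is √(0.7 × 0.3 / 330) = 0.025. The screening choice for mortality is therefore the more fragile one.

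**Power to see heterogeneity.** Take SE(AUC) = 0.037 and let the correlation between AUCs equal the inter-scale correlation. One paired difference contrasted between two settings has SE 2 × 0.037 × √(1 − 0.5) = 0.052, or 2 × 0.037 × √(1 − 0.7) = 0.041. For 80% power the true contrast must be about 2.80 × 0.041 = 0.115 to 2.80 × 0.052 = 0.146.

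**The case against.** The strongest reply has four parts.

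- **The index is not the AUC.** It includes the proportion evaluated. The tools range from a self-report questionnaire to an index that needs serum vitamin D, so completion may separate them. If completion differs between tools but not between settings, winners agree far more often, as shown. If completion truly differs by setting, different winners are real. This stands, and it limits the size of the point.
- **Death is the rarest of the four outcomes,** as the protocol says. Agreement improves for commoner ones. This stands too, except when scales are truly equal, where event rate makes no difference.
- **Separate analysis is defensible.** Barthel limits differ between nursing homes and the other settings, frailty prevalence differs, and each setting is sized for its own model. If all tools were equal, any choice would be equally accurate. This stands against replacing the per-setting analyses. It does not support presenting their differing maxima as setting-specific findings.
- **The SAP is not shown.** Interaction tests and intervals may be there, so their absence from an article is no error. But the article itself fixes the selection rule and its intended use, and those are what is questioned here.

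A reader might infer that nothing is compared across settings. The external-validity step contradicts that; it is only the wrong quantity for this choice and is not tied to it. A reader might also infer that stratifying throws away three quarters of the deaths. It does not: every death is analysed in its own setting.

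**Conclusion.** The concern holds in limited form. The maximum rule within each setting, carried into algorithms by setting, can yield chance-driven recommendations, and no described analysis tied to that choice estimates between-setting differences in ranking.

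For mortality ranked on AUC, four-setting agreement is under 1% if scales are equal and about 11 to 24% if one is uniformly better by 0.04. These figures rest on assumed AUCs and correlations, equal completion, and about 58 deaths per setting. They rank AUC and not the protocol's index.

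The tempting stronger claim, that chance is almost bound to produce different winners, is not supported. It is true only when scales are equal or nearly so. With a clear leader, highly correlated scales, commoner outcomes or clear differences in completion, agreement can be common (74% and 78 to 92% in the scenarios above).

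**What to change.** Keep the per-setting analyses. For each outcome, add a pooled estimate with confidence interval of the between-setting heterogeneity in paired differences between scales, computed on the protocol's own index. A bootstrap stratified by setting or a scale-by-setting interaction would do. Report it beside the pooled ranking.

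Describe a tool as specifically better for one setting only where these estimates support it. Otherwise report that setting's winner as not distinguishable from the pooled ranking. A non-significant interaction should not be read as proof of homogeneity, and it should not by itself force a single common tool: the power calculation above shows that modest heterogeneity would often be missed.

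The cost is a little more analysis of data that the study collects anyway. The downsides are limited power for modest heterogeneity and possibly a weaker conclusion about setting-specific tools.

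### Picking the most sensitive scale for screening and the most specific for diagnosis, with no common operating point, can favour a less discriminating scale

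*Protocol article*

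**What the plan says.** The Statistical analysis section plans, for every scale, setting and outcome, three logistic models (unadjusted; age and gender; age, gender and Charlson index), and "we will compute the classification performance (sensitivity, specificity, ROC curve, AUC, predictive values, likelihood ratios) for each model". It then turns this set of measures into a choice: "we will assess the most accurate scale for both screening (the most sensitive tool) and diagnostic purposes (the most specific tool". The choice is made "for each setting and for each outcome".

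A second step brings in feasibility: "Combining both outcomes by creating an index (classification performance * proportion of evaluated patients), we will determine the best scale (maximum value of the index". The text does not say which of the listed measures stands for classification performance in that product.

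Under Secondary outcomes, the item on qualification as a screening or diagnostic tool is broader. It aims to "evaluate the utility of each scale as a frailty detection method, using pre-established criteria, based on the prevalence of this condition in each setting", and lists sensitivity, specificity, predictive values, likelihood ratios, feasibility and sensitivity to change. It gives no thresholds and no link to the rule above.

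Of one of the seven scales, the Gérontopôle tool, the article says "There is no clear cut-off point to classify the patient as frail or not".

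**The concern.** Any score can be made more sensitive by lowering its cut-off, at the cost of specificity, and the reverse. Ranking scales on one of the two while leaving the other free therefore mixes two things: how well a scale separates people with and without the outcome, and how freely it flags people. Only the first is accuracy, yet the rule calls its winner the most accurate scale.

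At stake is the recommendation of a screening scale and a diagnostic scale for each setting, and the detection algorithms that the secondary objectives build on it. The AUCs and the association estimates themselves are not affected.

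**Working it through.** **Inputs from the protocol.** The Recruitment process and sample size section gives 10% annual mortality, so 10% × 1.5 years = 15% at 18 months, as stated. The evaluable numbers of 355 and 388 per setting also reproduce if 10 events per variable are assumed (4 × 10 = 40 events):
- n = 355: 53.25 − 1.96 × √(355 × 0.15 × 0.85) = 40.1.
- n = 388: 58.20 − 2.576 × √(388 × 0.15 × 0.85) = 40.1.
- 388 / 0.8 = 485, and 485 × 4 = 1940.

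The sample size is not in question. Only the 15% is used below.

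**Assumed inputs.** The article gives no AUCs and no flagged fractions. I take a better scale (AUC 0.75) and a weaker one (AUC 0.62), both equal-variance binormal. The separation is d = √2 × Φ⁻¹(AUC), which gives 0.954 and 0.432.

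**Formulas.** At cut-off c, sensitivity = 1 − Φ(c − d), specificity = Φ(c), and flagged fraction = 0.15 × sensitivity + 0.85 × (1 − specificity). Solve for c at a given flagged fraction.

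| Scale | Flags | Sensitivity | Specificity |
|---|---|---|---|
| AUC 0.75 | 20% | 0.47 | 0.85 |
| AUC 0.62 | 60% | 0.73 | 0.42 |
| AUC 0.62 | 10% | 0.18 | 0.91 |
| AUC 0.62 | 20% | 0.31 | 0.82 |

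Check of row 2: 0.15 × 0.734 + 0.85 × 0.576 = 0.60.

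- On the stated rule the weaker scale wins screening when it flags 60% (0.73 against 0.47) and diagnosis when it flags 10% (0.91 against 0.85).
- At equal flagged fractions (rows 1 and 4) the better scale wins both titles. Against a better scale flagging 20%, the weaker one overtakes on sensitivity once it flags more than about 33%, and on specificity once it flags less than about 17%.

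**Common operating point.** Sensitivity at specificity 0.80 is 1 − Φ(0.842 − d): 0.54 for AUC 0.75 and 0.34 for AUC 0.62. In this symmetric model, specificity at sensitivity 0.80 takes the same two values. The order is right for both purposes.

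**If performance is read from logistic predictions.** With one score and 15% events, a probability cut p corresponds to c = [logit(p) − logit(0.15) + d²/2] / d. For AUC 0.75, p = 0.5 gives sensitivity 0.09 and specificity 0.99, while p = 0.15 gives 0.68 and 0.68. The unstated probability cut-off then drives the figures.

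**Index at equal feasibility.** Suppose 90% are evaluated on both scales and sensitivity or specificity is the performance term. Screening: 0.9 × 0.73 = 0.66 against 0.9 × 0.47 = 0.42. Diagnosis: 0.9 × 0.91 = 0.82 against 0.9 × 0.85 = 0.76. The wrong order remains.

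**Likelihood ratios at fixed cut-offs.** LR− = (1 − sensitivity) / specificity. AUC 0.62 flagging 80% gives (1 − 0.889) / 0.216 = 0.52, which beats AUC 0.75 flagging 20% at (1 − 0.471) / 0.848 = 0.62. LR+ = sensitivity / (1 − specificity). AUC 0.62 flagging 2% gives 2.72, against 2.46 for AUC 0.75 flagging 30%. Ranking on these still depends on the cut-off.

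**The case against.** The strongest reply is that the quoted sentence does not stand alone. The qualification item under Secondary outcomes uses several measures for the same screening and diagnosis labels, including predictive values and likelihood ratios, which would expose a poor scale. The best scale per setting is named by the index, and classification performance there may mean something other than sensitivity or specificity. The article condenses a fuller plan, where thresholds may be set. This stands in part: either element could soften the problem. But the article does not say that either overrides the rule that it does state, so the two sections need reconciling.

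It is also fair that the illustration uses raw dichotomised scores, whereas the plan computes performance for each model. The figures show direction, not the size of error to expect. Moving to model predictions replaces the scale's cut-off with a probability cut-off and leaves the dependence in place.

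Two further inferences are tempting and go beyond the text. A reader might infer that the Gérontopôle cut-off will be tuned on these data and so favour that tool. The article says only that no clear cut-off exists, not how one will be chosen. A reader might also object that the reference is an adverse outcome while the Secondary outcomes promise that "The performance of each scale in the classification of frailty will be established". That is a separate matter: the primary outcome is openly the prediction of adverse outcomes, and the selection is made per outcome.

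Finally, choosing the best scale is a secondary objective, and the primary predictive results do not depend on this rule. That limits the reach of the problem without removing it.

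**Conclusion.** The concern holds as a flaw in the stated selection rule. With one error rate maximised and the other free, a less discriminating scale can be named best for screening or diagnosis. In the illustration, AUC 0.62 beats AUC 0.75 by 0.73 to 0.47 on sensitivity or by 0.91 to 0.85 on specificity, while a common specificity of 0.80 restores the order at 0.54 to 0.34.

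This rests on assumed AUCs and flagged fractions, on binormal scores, and on the scales flagging clearly different fractions or the models being cut at different probabilities. At equal flagged fractions the rule picks the better scale.

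A reader might infer that a useless scale will win, or that the rule always rewards whichever scale flags most or fewest people. The first is arithmetically possible: a scale unrelated to the outcome that flags 60% has sensitivity 0.60, above 0.47. But nothing in the article suggests that any of the seven is uninformative. It credits the frailty phenotype and the Clinical Frailty Scale with predictive value, and it plans to assess each scale's association with the outcome. The second is a tendency, not a certainty.

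**What to change.** Replace the selection sentence in the Statistical analysis section. For screening, rank scales by sensitivity at one common specificity. For diagnosis, rank them by specificity at one common sensitivity. Read both from the ROC curve of each ordinal score, the Gérontopôle score included, so that no scale needs a cut-off of its own. Fix the two common values before any ROC curve is examined; the 0.80 above is only illustrative. State that this value is the classification-performance term in the index. Then say how the criteria in the qualification item under Secondary outcomes relate to this choice, with their thresholds.

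Do not substitute a ranking by LR− or LR+ at published cut-offs, for the reason shown in the working. Report likelihood ratios alongside.

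The cost is a change of wording; the data and the planned ROC output stay the same. The real downside is that scales with few levels need interpolation along the ROC curve, and an interpolated point is not a cut-off that can be applied in practice. Performance at the published cut-offs, where they exist, should therefore be reported as well.
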